## Abstract

**Introduction:**

HIV remains underdiagnosed. Guidelines recommend routine HIV testing in primary care, but evidence on implementing testing is lacking. In a previous study, the Rapid HIV Assessment 2 (RHIVA2) cluster randomised controlled trial, we showed that providing training and rapid point-of-care HIV testing at general practice registration (RHIVA2 intervention) in Hackney led to cost-effective, increased and earlier diagnosis of HIV. However, interventions effective in a trial context may be less so when implemented in routine practice. We describe the protocol for an MRC phase IV implementation programme, evaluating the impact of rolling out the RHIVA2 intervention in a post-trial setting. We will use a longitudinal study to examine if the post-trial implementation in Hackney practices is effective and cost-effective, and a cross-sectional study to compare Hackney with two adjacent boroughs providing usual primary care (Newham) and an enhanced service promoting HIV testing in primary care (Tower Hamlets).

**Methods and analysis:**

Service evaluation using interrupted time series and cost-effectiveness analyses. We will include all general practices in three contiguous high HIV prevalence East London boroughs. All adults aged 16 and above registered with the practices will be included. The interventions to be examined are: a post-trial RHIVA2 implementation programme (including practice-based education and training, external quality assurance, incentive payments for rapid HIV testing and incorporation of rapid HIV testing in the sexual health Local Enhanced Service) in Hackney; the general practice sexual health Network Improved Service in Tower Hamlets and usual care in Newham. Coprimary outcomes are rates of HIV testing and new HIV diagnoses.

**Ethics and dissemination:**

The chair of the Camden and Islington NHS Research Ethics Committee, London, has endorsed this programme as an evaluation of routine care. Study results will be published in peer-reviewed journals and reported to commissioners.

Strengths and limitations of this studyThe study will use existing trial data preceding the implementation programme in addition to post-trial data, collected using similar methods to those used in the trial.Fully anonymised general practice data from all participating boroughs will be remotely extracted using a single general practice computer system (Egton Medical Information Systems, EMIS).A large dataset with at least 12 time points before and at least 29 time points after the intervention implementation will provide precise estimation of the effects of intervention using interrupted time series analysis.Differences in HIV testing protocols, data quality and extraction between Hackney, and Tower Hamlets and Newham; and previous interventions such as rapid HIV testing pilots in a small number of Newham practices, may affect comparability between boroughs. Also, cross-contamination of Rapid HIV Assessment 2 (RHIVA2) control practices from intervention practices, or between boroughs, may have occurred.Finally, the post-trial implementation programme of the RHIVA2 intervention differed slightly from the research intervention to account for the complexities of delivering services in routine healthcare settings.

## Introduction 

HIV prevalence is increasing, with over 100 000 people now estimated to be living with HIV in the UK.^1^ From 1999 to 2013, the numbers of patients accessing specialist care increased fourfold.^2 3^ Successfully treated, HIV now has characteristics of a long-term condition, with patients taking lifelong treatment and increasingly exhibiting age-related comorbidities, such as cardiovascular disease, osteoporosis and mental illness. The cost of HIV care for the National Health Service (NHS) (without considering the cost of treating comorbidities) in 2013 was estimated to be £750 million (£1billion with social care included).^4^

Late diagnosis of HIV increases morbidity and mortality, and is associated with unwitting onward transmission. To reduce the pool of undiagnosed infection in the population, the British HIV Association (BHIVA) and National Institute for Health and Care Excellence (NICE) recommended expansion of routine HIV testing from sexual health and antenatal clinics to non-traditional settings including general practices located in high HIV prevalence areas (two or more people diagnosed with HIV/1000 adult population).^5–8^ In the Framework for Sexual Health Improvement in England (2013), the UK Department of Health additionally set out recommendations for the commissioning of HIV testing in high prevalence areas across all healthcare settings, including general practice.^9^ However, the decision to implement these recommendations lies with the 74 local authorities in England and the respective clinical commissioning groups (CCGs). Although National Policy for HIV screening in antenatal settings has proven highly effective, guidance for screening in general practice is lacking. Indeed, it was hoped that recommending routine HIV testing would suffice to enhance awareness of HIV among general practitioners (GPs) and become standard in this setting.^10^ Pilot studies have demonstrated feasibility and acceptability of routine HIV testing among patients and healthcare professionals.^11 12^ Despite this, a recent systematic review identified low uptake of routine HIV testing in non-traditional UK settings including general practice following the BHIVA 2008 guidelines.^13^

In a large-scale pragmatic cluster randomised controlled trial (Rapid HIV Assessment 2 (RHIVA2)) in the London borough of Hackney, we showed that rapid HIV testing offered at general practice registration was effective and safe, and delivered increased and earlier HIV diagnosis.^14^ Furthermore, a recent health economics analysis of the RHIVA2 trial demonstrated that HIV screening in primary care in high HIV prevalence areas is cost-effective.^15^ Following completion of this trial, we implemented HIV testing into routine care across all Hackney practices using a theory-based programme^16–18^ comprising an adaptation of the RHIVA2 intervention, including a practice-based education programme, a borough-wide audit of HIV care, and the introduction of payments for routine HIV testing as part of an updated general practice sexual health Local Enhanced Service (LES).^19^

We will evaluate both the RHIVA2 trial and post-trial implementation programme through an MRC phase IV implementation study.^20^ The study will also compare the impact of RHIVA2 implementation in Hackney practices with two neighbouring boroughs; Tower Hamlets that offers a general practice sexual health Network Improved Service (NIS) promoting routine HIV testing; and Newham offering usual primary care without incentivised HIV testing.

Figure 1 summarises the timelines of HIV-related interventions in these three boroughs.

**Figure 1 F1:**
[figure not shown]
Sexual health service provision in East London general practice. In Hackney (blue), the Rapid HIV Assessment (RHIVA) research programme promoting rapid point-of-care HIV testing was developed in addition to a sexual health local enhanced service (LES) and included: a pilot study (RHIVA1), a cluster randomised controlled trial across 20 intervention practices (RHIVA2) and implementation of the RHIVA2 intervention across all Hackney practices. In April 2013, the RHIVA2 intervention was integrated with the sexual health LES. In Tower Hamlets (red), a sexual health network improved service (NIS) replaced the previous LES in April 2011. Newham (green) does not provide a service promoting HIV testing (usual care). BHIVA, British HIV Association; DoH, Department of Health; NICE, National Institute for Health and Care Excellence.

The study will therefore address the following questions:How effective and cost-effective is the RHIVA2 intervention when implemented as a clinical service outside a research context?How do effectiveness and cost-effectiveness of the RHIVA2 trial and implementation programme compare with a borough-wide sexual health NIS promoting routine HIV testing in Tower Hamlets?How do both the RHIVA2 trial and post-trial implementation programme and the Tower Hamlets sexual health NIS compare with Newham that offers usual HIV primary care only?

## Methods and analysis

### Setting

The study will be set in the three East London boroughs of Hackney, Tower Hamlets and Newham. The estimated diagnosed HIV prevalence for these boroughs is 8.1, 6.5 and 6.7 per 1000 adult population, respectively.^21^ We will include all adults aged 16 and above registered with general practices in the three boroughs.

### Design

Service evaluation comprising a pragmatic cohort using an interrupted time series (ITS) analysis and cost-effectiveness analysis. The evaluation will examine the longitudinal impact of interventions in Hackney and the comparative cross-sectional impact of interventions in Hackney, Tower Hamlets and Newham. HIV testing and diagnosis data from 1 April 2009 to 30 June 2015 is being collected.

### Interventions

#### Hackney

The RHIVA2 intervention was first introduced in April 2010 in 20 general practices randomised to the intervention arm of the RHIVA2 trial (table 1). This theory-based intervention^16–18^ is described in detail in Leber *et al*^14^ and consisted of a practice-based educational training session for the primary care team to promote rapid HIV testing at registration, a follow-up meeting with a nominated practice lead nurse, integration of rapid HIV testing with the general practice computer template, and an incentive payment of £10 per rapid HIV test performed. Testing competence was monitored by an external quality assessment. This intervention was offered in addition to an existing national antenatal HIV screening service offered at the practices, and a sexual health LES promoting sexual health screening including HIV case detection (incentive payments of £265 per newly diagnosed patient) introduced in 2006/2007.^19^

**Table 1 T1:** Schedule for enrolment, interventions and assessment of the study

Timepoint	Study period									
	Control period			Practice allocation	Post-allocation			Close-out		
	−41 months	−24 months	−12 months	0 months	+1 months	+2 months	≥12 months	+29 months	+34 months	+51 months
RHIVA2 trial:			X							
Allocation				X						
Intervention					X					
Enrollment						X	X	X		
RHIVA2 post-trial implementation:	X									
Allocation				X						
Intervention					X					
Enrollment						X	X	X	X	
Tower Hamlets:		X								
Allocation				X						
Intervention				X						
Enrollment				X	X	X	X	X	X	X
Assessments:										
HIV testing	X	X	X	X	X	X	X	X	X	X
HIV diagnosis	X	X	X	X	X	X	X	X	X	X

RHIVA2, Rapid HIV Assessment 2.

The RHIVA2 post-trial implementation programme ran from September 2012 to June 2015 and comprised the following three components^16–18^:Additional post-trial HIV testing training (September 2012 to February 2013). This was offered to all Hackney practices at the completion of the RHIVA2 trial and comprised a modification of the RHIVA2 trial intervention whereby practices were encouraged to offer both routine serology and rapid HIV testing in any clinical setting (rather than just rapid testing at practice registration).Updated sexual health LES. From April 2013, the existing LES was replaced with HIV testing payments to practices of between £7 and £10 for every rapid or serology HIV test carried out in any clinical setting, in addition to a payment of £258 for any new diagnosis.General practice-based HIV care audit (October 2012 to March 2013) of missed diagnoses of HIV and safety of coprescribing with antiretroviral medication in Hackney general practices.^22^

#### Newham

*Usual care*—no specific borough-wide initiatives were promoted relating to HIV testing in primary care.

The RHIVA2 intervention is based on published clinician behaviour change programmes,^16–18^ and the Tower Hamlets NIS follows Royal College of General Practitioners guidance on establishing general practice federations.^23^ We will report our study in accordance with the STARI reporting guidelines for implementation studies.^24^

### Outcome measures

All data gathered will comprise routine clinical data. No identifiable data will be held by the research team.

#### Coprimary outcome measures

Rates of HIV testing (combined rapid and serology testing; number of patients tested/1000 population/year)Rates of new HIV diagnosis (number of newly diagnosed patients/10 000/year)

#### Secondary outcome measures

Secondary outcome measures will include data on type of HIV test (serology; rapid), location of diagnosis, stage of disease and linkage to secondary care and retention in secondary care:Number/rate of patients who received a rapid HIV test.Number/rate of patients who received a serology HIV test.Number/rate of patients newly diagnosed in general practice.Mean and median CD4 count of patients newly diagnosed in primary care.Proportion of patients with a CD4 count <350 cells/μL of blood.Proportion of patients with a CD4 count <200 cells/μL of blood.Proportion of patients newly diagnosed with HIV in primary care who attend an HIV specialist department within 1 week of diagnosis.Proportion of patients newly diagnosed with HIV in primary care who attend an HIV specialist department within 2 weeks of diagnosis (BHIVA Standards of Care for people living with HIV (PLHIV), Standard 2, 2013).^25^Proportion of patients newly diagnosed with HIV in primary care who attend an HIV specialist department within 4 weeks of diagnosis (NHS England Standard).Proportion of patients newly diagnosed with HIV in primary care who attend a HIV specialist department within 3 months of diagnosis (Optimising testing and linkage to care for HIV across Europe, OptTEST, 2013).Number of patients previously known to have HIV, who attend an HIV specialist clinic between 12 and 24 months following new diagnosis in primary care (BHIVA Standards of Care for PLHIV, Standard 2, 2013).

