### Data sources

We will gather data from April 2009 to June 2015 using the following sources.

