#### Clinical data

##### HIV diagnosis data

Borough-specific master case report forms (CRF) containing lists of patients with a positive confirmatory HIV test result will be generated by the lead HIV clinician from the clinical HIV services in each borough. This master CRF will be shared with the study team in an anonymised format as per the RHIVA2 protocol. At Homerton Hospital, Hackney data on newly diagnosed patients have been collected prospectively as outlined in RHIVA2 (continuous data available from 2009). For Tower Hamlets and Newham, new diagnosis data will be collected retrospectively for the same period. Clinical leads will liaise with Public Health England to categorise patients with a positive confirmatory HIV test into newly diagnosed patients and people already known to be HIV positive, and obtain data on patients who had defaulted from care between 12 and 24 months following diagnosis.

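### The only retention outcome has a self-contradictory population and no denominator, and its 12 to 24 month window is cut off after the interventions if attendance data end in June 2015

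*Protocol article*

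**What the plan says.** The section Secondary outcome measures announces data on, among other things, "linkage to secondary care and retention in secondary care". Four items then cover linkage. All are proportions of newly diagnosed patients, for example "Proportion of patients newly diagnosed with HIV in primary care who attend an HIV specialist department within 1 week of diagnosis". The testing and diagnosis items are given as number or rate, for example "Number/rate of patients newly diagnosed in general practice". Retention has one item, the last in the list: "Number of patients previously known to have HIV, who attend an HIV specialist clinic between 12 and 24 months following new diagnosis" in primary care.

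The section HIV diagnosis data says that clinical leads will work with Public Health England to "categorise patients with a positive confirmatory HIV test into newly diagnosed patients and people already known to be HIV positive". The same sentence adds that they will "obtain data on patients who had defaulted from care between 12 and 24 months following diagnosis".

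On timing, Data sources opens with "We will gather data from April 2009 to June 2015 using the following sources", and the HIV clinic lists are among those sources. The Design section gives the same end date, 30 June 2015, but attaches it to testing and diagnosis data. No section states a later end for clinic attendance or limits the retention item to earlier diagnoses.

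**The concern.** Three features stop this item from measuring retention.

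- **Population.** The item selects people whose HIV was already known but starts the clock at a new diagnosis. Under the plan's own categories nobody is in both groups. One analyst could report retention of newly diagnosed patients and another could report re-engagement of known positives who tested again in primary care. These are different patients and different questions.
- **Metric.** A count of attenders mixes the number diagnosed with the share retained. The programmes aim to raise the number diagnosed, and the periods and boroughs differ in length and size.
- **Follow-up.** The window closes 24 months after diagnosis. If attendance data stop when diagnosis data stop, the most recent diagnoses are not fully observed, and all of these fall after the interventions in Hackney and Tower Hamlets.

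At stake is the plan's only evidence on whether people diagnosed in primary care stay in specialist care.

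**Working it through.** **Inputs.** Data run from April 2009 to June 2015 (Design; Data sources). The Hackney programme ran from September 2012 to June 2015, with training from September 2012 to February 2013 (Interventions, Hackney). The Tower Hamlets Network Improved Service (NIS) began in April 2011 (Interventions, Tower Hamlets). The retention window is months 12 to 24 after diagnosis.

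**The plan's own time points (Sample size).**
- April 2009 to June 2015: 6 × 12 + 3 = 75 months.
- Before Hackney implementation, April 2009 to August 2012: 3 × 12 + 5 = 41. The plan says 41.
- From February 2013, the last training month, to June 2015: 11 + 12 + 6 = 29. The plan says a minimum of 29.
- From September 2012 to June 2015: 75 − 41 = 34.
- Tower Hamlets before, April 2009 to March 2011: 24. After: 75 − 24 = 51. The plan says 24 and a minimum of 51.

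All stated figures reproduce, which confirms June 2015 as the last month of the series.

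**Window cut-offs, assuming attendance data also end on 30 June 2015.**
- Complete window: diagnosis + 24 months ≤ June 2015, so diagnosis by the end of June 2013.
- Month 12 reached at all: diagnosis + 12 months ≤ June 2015, so diagnosis by the end of June 2014.
- Partial: July 2013 to June 2014, 12 months. None: July 2014 to June 2015, 12 months.

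| Diagnosis period | Months | Complete | Partial | None |
|---|---|---|---|---|
| Whole series | 75 | 51 (68%) | 12 (16%) | 12 (16%) |
| Hackney before implementation | 41 | 41 (100%) | 0 | 0 |
| Hackney from September 2012 | 34 | 10 (29%) | 12 (35%) | 12 (35%) |
| Hackney practice trained in February 2013 | 29 | 5 (17%) | 12 (41%) | 12 (41%) |
| Tower Hamlets before NIS | 24 | 24 (100%) | 0 | 0 |
| Tower Hamlets after NIS | 51 | 27 (53%) | 12 (24%) | 12 (24%) |

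The last pre-implementation month in Hackney, August 2012, closes its window in August 2014, so that whole period is complete.

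**What this does to a count.** Write the monthly count as D × p × s, where D is diagnoses per month, p the share retained and s the share of diagnoses that can be observed. Before Hackney implementation s = 1. From September 2012, with diagnoses evenly spread, s lies between 10/34 = 0.29 (complete windows only) and (10 + 12)/34 = 0.65 (every partial window still yields its attendance). With p unchanged, the average monthly count stays level only if D rises by a factor between 34/22 = 1.5 and 34/10 = 3.4. A smaller rise lowers the count and a larger one raises it, and neither says anything about p.

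**The case against.** The strongest reply concerns the cut-off. Design ties June 2015 to testing and diagnosis data only, and the opening line of Data sources can be read as the period for those events. The item on defaulters carries no end date. The text describes the programme as already finished in June 2015, so later attendance data could exist. This stands as a reason to make the truncation conditional. It does not remove it: no section gives a later attendance cut-off, and for Tower Hamlets and Newham the Discussion says outcomes of newly diagnosed people are being extracted for the specified study period.

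Second, a proportion could be built from planned data, because new diagnoses in general practice are a listed outcome and defaulters are the complement of attenders. That shows the repair is cheap. It does not make the stated outcome a proportion, and the complement works only once the population is fixed.

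Third, the stated population might mean patients diagnosed 12 to 24 months earlier and known by then. This is possible but strained, given the two categories in HIV diagnosis data. The defaulter data suggest that retention of newly diagnosed patients was meant, but do not settle it.

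A reader might also infer more than the documents support:
- That the count must fall after implementation. It need not, because diagnoses may rise.
- That the programme will be shown to retain patients less well. The interrupted time series analyses are specified for testing and diagnosis, and no before-and-after analysis of retention is set out.
- That the percentages above are shares of patients. They are shares of calendar months, since the article gives no monthly diagnosis counts.

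**Conclusion.** The outcome is badly defined and should be restated. Two parts hold without any assumption: the population conflicts with the start point, and a bare number cannot compare retention across periods or boroughs.

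The third part is conditional. If attendance data end in June 2015, 24 of 34 Hackney implementation months (71%) and 24 of 51 Tower Hamlets post-NIS months (47%) lack a complete window, against none of the 41 and 24 months before. The two programmes would thus be truncated to different degrees. The post-intervention count is then biased downward relative to complete follow-up. The Hackney figure counts from September 2012; for a practice trained in February 2013 it is 24 of 29 (83%). These equal shares of diagnoses only if diagnoses are evenly spread.

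This is one secondary outcome. The coprimary rates of testing and new diagnosis are not touched.

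**What to change.** Restate the outcome as the proportion of patients newly diagnosed with HIV in primary care who attended an HIV specialist clinic between 12 and 24 months after diagnosis. State the attendance data cut-off, then do one of the following:

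1. Limit the denominator to patients whose 24-month window closes by that cut-off, which means diagnosis by 30 June 2013 if the cut-off is June 2015.
2. Extend the routine attendance data to 24 months after the last included diagnosis.

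Apply the same rule in every borough and period. If re-engagement of people already known to be HIV positive was also intended, report it as a separate outcome with its own start date.

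The change is one of definition. Option 1 costs post-implementation patients in this outcome: 10 of 34 diagnosis months remain in Hackney and 27 of 51 in Tower Hamlets. Option 2 costs a further extraction of routine data.
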